## Abstract

**Background:**

Some Chinese scholars have initially explored the efficacy of electroacupuncture at Baliao acupoint in patients with functional anorectal pain (FAP). However, their studies are performed in a single center, or the sample size is small. Therefore, we aim to further explore the efficacy of electroacupuncture at Baliao acupoint on the treatment of FAP.

**Methods:**

In this multicenter randomized controlled trial, 136 eligible FAP patients will be randomly allocated into an electroacupuncture group or sham electroacupuncture group at a 1:1 ratio. This trial will last for 34 weeks, with 2 weeks of baseline, 4 weeks and 8 weeks of treatment, and 1, 3, and 6 months of follow-up. Outcome assessors and statisticians will be blind. The primary outcome will be clinical treatment efficacy, and secondary outcomes will be pain days per month, quality of life, psychological state assessment, anorectal manometry, pelvic floor electromyography, and patient satisfaction.

**Discussion:**

Results of this trial will be contributed to further clarify the value of electroacupuncture at Baliao acupoint as a treatment for FAP in the clinic.

**Trial registration:**

This trial has been registered in Chinese Clinical Trial Registry https://www.chictr.org.cn/ (ChiCTR2300069757) on March 24, 2023.

**Supplementary Information:**

The online version contains supplementary material available at 10.1007/s00384-024-04628-5.

## Introduction

Functional anorectal pain (FAP) is an unexplained and nonorganic pain [1]. Rome IV categorized FAP into three types: proctalgia fugax, levator ani syndrome, and unspecified functional anorectal pain [2]. The latter two types are distinguished by whether there is traction pain on the puborectalis [3]. The prevalence of anorectal pain caused by all reasons or levator ani syndrome is 11.6% and 6.6%, respectively [3]. FAP patients often have mental and emotional disorders, which seriously affect their mental health and quality of life [4].

The pathophysiology of FAP remains unclear. Excessive contraction and high tension of pelvic floor muscle have been widely believed as one of the possible mechanisms [4]. A study has indicated that levator ani syndrome was closely associated with the pelvic floor spasm [5]. In addition, paroxysmal anal hypermobility was reported as an important feature of proctalgia fugax [6]. At present, a range of interventions have been reported for FAP, such as medications, biofeedback, electrogalvanic stimulation (EGS), botulinum toxin injection, and sacral nerve modulation (SNM) [1, 3]. A recent meta-analysis indicated that acupuncture should be considered a new and alternative intervention in future studies [7].

Acupuncture at Baliao acupoint has been reported to treat pelvic floor dysfunctions [8, 9]. Shen et al. have found that the level of anal pain and incidence of urinary retention were lower after the electroacupuncture at Baliao acupoint than the control in patients undergoing stapled hemorrhoidopexy [8]. Liu et al. have reported that electroacupuncture at Baliao acupoint significantly improved bladder capacity and compliance in patients with detrusor overactivity after stroke and reduced detrusor leak point pressure [9]. In China, some scholars have initially investigated the effect of electroacupuncture at Baliao acupoint on FAP [10, 11]. It had been reported that electroacupuncture at Baliao acupoint was superior to biofeedback in efficacy, visual analogue scale (VAS) score, and quality of life [10]. The study of Yu et al. showed that electroacupuncture at Baliao acupoint combined with biofeedback significantly promoted the clinical efficacy and decreased the VAS score compared to biofeedback alone [11]. Because of the small sample size or the single center of these studies [10, 11], the efficacy of electroacupuncture at Baliao acupoint in the treatment of FAP needs to further explore.

Considering this, this study aims to further explore the effect of electroacupuncture at Baliao acupoint on the treatment of FAP through a larger sample size, multicenter, randomized controlled trial.

## Methods

### Study design

This is a multicenter, paralleled, randomized, controlled trial. The eligible patients will be randomly divided into the treatment group (electroacupuncture group) and control group (sham electroacupuncture group) at a 1:1 ratio. This study will last for 34 weeks, including 2 weeks before randomization (baseline), 8 weeks of treatment, and 24 weeks of follow-up. Follow-up will be conducted at baseline, 4 weeks of treatment, 8 weeks of treatment, and 1 month (12 weeks), 3 months (20 weeks), and 6 months (32 weeks) after the treatments. This study protocol conforms to the Consolidated Standards of Reporting Trials (CONSORT) [12] and Standards for Reporting Interventions in Clinical Trials for Acupuncture (STRICTA) [13]. This study followed the Declaration of Helsinki and has been approved by the Institutional Review Board of Nanjing Hospital of Chinese Medicine Affiliated to Nanjing University of Chinese Medicine, Longhua Hospital of Shanghai University of Traditional Chinese Medicine, Yinchuan Traditional Chinese Medicine Hospital, and Suzhou Hospital of Traditional Chinese Medicine Affiliated to Nanjing University of Chinese Medicine, approval no. KY2023012. Written consent form will be obtained from all patients. This study has been registered in the Chinese Clinical Trial Registry (registration no. ChiCTR2300069757) on March 24, 2023. The details of study design are demonstrated in Fig. 1, and the trial schedule is presented in the Supplementary information Table 1.

**Fig. 1 Fig1:**
[figure not shown]
Flowchart showing the selection process of FAP patients

### Participants

Patients will be recruited from the outpatient clinic and inpatients in the Anorectal Department of Nanjing Hospital of Chinese Medicine Affiliated to Nanjing University of Chinese Medicine, Longhua Hospital of Shanghai University of Traditional Chinese Medicine, Yinchuan Traditional Chinese Medicine Hospital, and Suzhou Hospital of Traditional Chinese Medicine Affiliated to Nanjing University of Chinese Medicine. The recruitment strategies include putting up posters and distributing information on the WeChat Public Platform (the largest social media platform in China). All patients will be informed of the details of the study (objective, procedure, and potential risks) in written form, and the informed consent will be signed before the allocation.

### Inclusion criteria

Patients meeting the following criteria will be included: (1) meeting the diagnostic criteria of levator ani syndrome and unspecified functional anorectal pain (Rome IV criteria), (2) with chronic or recurrent FAP (pain lasting for at least 30 min each time, occurring at least once a week, and presenting ≥ 6 months), (3) aged 20–70 years old, (4) not receiving acupuncture treatment within 3 months before the enrollment, and (5) voluntarily participating in this study and signing the informed consent form.

Levator ani syndrome is diagnosed as the following criteria: chronic or recurrent rectal pain, lasting for at least 30 min, traction pain on puborectalis, excluding other causes of rectal pain, such as inflammatory bowel disease, intramuscular abscess or anal fissure, thrombotic hemorrhoids, and prostatitis. Unspecified functional anorectal pain is diagnosed as the following criteria: meeting the diagnostic criteria for levator ani syndrome but not presenting traction pain on puborectalis.

### Exclusion criteria

Patients will be excluded if they are (1) with pain caused by organic diseases, such as anal fissure, perianal abscess, and hemorrhoids; (2) with a history of anal and pelvic floor surgery within the past year; (3) with a history of pelvic and spinal cord injuries; (4) with severe cardiovascular, cerebrovascular, liver, kidney, respiratory, and hematopoietic diseases or malignant tumors; (5) taking anti-anxiety or anti-depression drugs to control illness (for the past 3 months), or currently combining with mental illness (confirmed); and (6) pregnant, lactating, and menstrual women.

### Elimination criteria

Patients will be eliminated if they are (1) mistakenly included patients who do not meet the inclusion criteria; (2) patients who had not been treated according to the protocol specified in this study, and with incomplete basic information and condition information, which affects the evaluation of clinical efficacy and safety; (3) patients with poor compliance and voluntarily withdrawing during the treatment process; and (4) patients using the prohibited treatment methods in this study protocol or changing the treatment methods themselves during the treatment process.

After the subject is eliminated, the supervising doctor will contact the subject by phone calls or letters to inquire about the reasons, record the time of the last treatment, and complete the assessment items that can be completed. For subjects withdrawn from the trial due to adverse reactions or ineffective treatment, the supervising doctor will take corresponding measures based on the actual situation. Intention-to-treat analysis will be conducted on all subjects who are eliminated or lost to follow-up after the end of the trial.

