### Criteria for discontinuing the trial

The trial will be discontinued if the following conditions occur: (1) patients exhibit serious adverse reactions during the study and are not suitable to continue the study; (2) patients require emergency measures for the reason that serious complications are presented or the condition is worsened during the study; (3) patients withdraw from the clinical study midway; and (4) patients do not cooperate and obey the treatment, which is not changed after repeated explanations from clinical doctors. The reasons and time for the discontinuation and withdrawal should be recorded by researchers.

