### Adverse event

The adverse reactions such as needle fainting, needle sticking, needle bending, and needle breaking during the electroacupuncture treatment, as well as adverse events such as empyrosis and getting blisters during the moxibustion, should be recorded. All adverse events should be treated appropriately based on the patient’s condition until the condition is stabilized. The adverse events can be processed by one or more of the following: taking no measures (mainly observation); adjusting electroacupuncture treatment measures such as reducing treatment frequency, reducing stimulation, and temporarily or permanently discontinuing electroacupuncture treatment; and providing non-drug therapies.

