#### Sample size calculation

The sample size is calculated based on the previous study [19]. This study assumes a 70% effective rate in the electroacupuncture group and a 40% effective rate in the sham electroacupuncture group. *α* is taken as 0.05, and 1- *β* (power) is taken as 0.9. PASS 11.0 software (NCSS, LLC. Kaysville, Utah) is used to calculate the sample size, and 57 subjects will be required for each group. Considering a 15% dropout rate, 67 subjects are required for each group, and a total of 134 subjects are required. Due to the sample size jointly responsible by 4 centers and block randomization, each center will provide 34 subjects, and a total of 136 subjects are required.

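### The elimination rule does not secure outcome collection after patients stop or deviate, and it misdescribes the intention-to-treat set that the plan promises

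*Protocol article*

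**What the plan says.** Elimination criteria in the protocol article has four grounds. The first is mistaken inclusion. The other three depend on what happens after allocation:

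- "patients who had not been treated according to the protocol specified in this study, and with incomplete basic information and condition information", where this affects the evaluation of efficacy and safety;
- "patients with poor compliance and voluntarily withdrawing during the treatment process";
- "patients using the prohibited treatment methods in this study protocol or changing the treatment methods themselves during the treatment process".

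After elimination, the supervising doctor phones or writes to ask for the reasons, and is to "record the time of the last treatment, and complete the assessment items that can be completed". The section foresees withdrawal for adverse reactions and for lack of effect. It closes with: "Intention-to-treat analysis will be conducted on all subjects who are eliminated or lost to follow-up after the end of the trial".

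Much of the same ground is covered again under Criteria for discontinuing the trial, for example "patients withdraw from the clinical study midway". Randomization and blinding says that patients and operators are difficult to blind, so only outcome assessors and statisticians are. Primary outcome schedules VAS at baseline, weeks 4 and 8 of treatment, and 1, 3 and 6 months of follow-up. Adverse event permits "adjusting electroacupuncture treatment measures such as reducing treatment frequency, reducing stimulation, and temporarily or permanently discontinuing electroacupuncture treatment". Sample size calculation states: "Considering a 15% dropout rate, 67 subjects are required for each group".

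**The concern.** Two things are fixed badly in the text itself.

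First, the closing sentence attaches intention-to-treat to the eliminated and lost patients. The term describes an analysis of everyone randomised, in the arm assigned. As written, the sentence leaves open what elimination removes a patient from, and two statisticians could build different primary sets from it.

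Second, the follow-up described after elimination is whatever can be completed. Nothing says that the remaining VAS visits, pain logs and SF-36 assessments go ahead. This is a matter of trial conduct: an analysis plan can choose how to treat a missing outcome but cannot create an observed one.

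The grounds for elimination are related to tolerability and response, and patients will often know or guess their arm. The missing outcomes may therefore be neither random nor balanced. At stake is how far the promised ITT result depends on observed data and how far on assumptions about patients who left.

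**Working it through.** **Inputs.** From Sample size calculation: effective rates of 70% (electroacupuncture) and 40% (sham), α = 0.05, power 0.90, 57 per group, 15% dropout, 67 per group, 136 in total. With 1:1 allocation, 136 / 2 = 68 per group. The plan gives no elimination rate, so its 15% dropout figure stands in for the share unobserved. That is an assumption.

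**Step 1. Reproduce the plan's figure.** Two-sided comparison of two proportions, pooled variance under the null, no continuity correction, mean rate (0.70 + 0.40)/2 = 0.55:

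n = [1.960 × √(2 × 0.55 × 0.45) + 1.282 × √(0.70 × 0.30 + 0.40 × 0.60)]² / 0.30² = (1.379 + 0.860)² / 0.09 ≈ 55.7, so 56 per group.

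The plan's 57 is within rounding of this and gives power of 90.7%. Inflation: 57 / 0.85 = 67.06, stated as 67. With 68 per group and 15% lost at random, 68 × 0.85 = 57.8 remain and power is 91.1%. The stated sample size is sound on this point.

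**Step 2. How much the unobserved patients could matter.** Let 15% per arm be unobserved and the other 85% respond at the planned rates. Observed responders, as a share of all randomised:

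- electroacupuncture: 0.85 × 0.70 = 0.595
- sham: 0.85 × 0.40 = 0.340

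The unobserved 15% can add between 0 and 0.15 to either arm.

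- Least favourable: 0.595 − (0.340 + 0.15) = 0.105
- Most favourable: (0.595 + 0.15) − 0.340 = 0.405

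The difference among all randomised patients lies between 10.5 and 40.5 points. The width of 30 points equals the planned effect itself. These are extreme bounds, not a forecast.

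**Step 3. Illustration under one simple rule.** Suppose missing outcomes count as not effective; this is an assumed rule, not the plan's. The formula is

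power = Φ{[d√n − 1.960 × √(2p̄(1 − p̄))] / √(p₁(1 − p₁) + p₂(1 − p₂))}

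with n = 68, p₁ = 0.595, p₂ = 0.340, d = 0.255 and p̄ = 0.4675:

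(2.103 − 1.383) / 0.682 = 1.055, so power is 85.4%. Exact enumeration of the chi-square test gives 85.1%.

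Imbalance in the missing share has a large effect under the same rule:

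| Missing, electroacupuncture / sham | Rates | Difference | Power |
|---|---|---|---|
| 15% / 15% | 59.5% vs 34.0% | 25.5 points | 85.4% |
| 15% / 5% | 59.5% vs 38.0% | 21.5 points | 71.3% |
| 5% / 15% | 66.5% vs 34.0% | 32.5 points | 97.4% |

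The unequal splits are assumed. They show that the direction of any distortion depends on which arm loses more patients, and the document does not settle that.

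**Step 4. What the text settles about eliminated patients.**

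- Do they leave the analysis? No section says so, and the closing sentence points to keeping them.
- Do their scheduled visits continue? No section says that they do, and none says that they stop.
- Is the ITT set all randomised patients as allocated? The sentence does not say this.

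**The case against.** The best defence is that the closing sentence is evidently meant to keep eliminated and lost patients in the analysis, which guards against the bias feared. A condensed article may also leave analysis sets and missing-data rules to a full protocol or analysis plan that is not shown. Both points stand. The absence of an imputation rule is not part of this finding. The defence does not cover the misworded sentence or the missing commitment to collect data.

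Several stronger readings are tempting but not supported:

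- *Eliminated patients are seen only once more.* The text sets no number of contacts and asks for whatever assessments can be completed.
- *The ITT analysis cannot be done.* Baseline VAS and any values before elimination exist, and with a stated missing-data rule the analysis can be computed, as Step 3 shows.
- *The Adverse event section contradicts the elimination list.* The off-protocol ground also requires incomplete information, and the changed-treatment ground concerns changes that patients make themselves. Adjustments that the protocol allows are not plainly departures from it. A clarification is enough.
- *The sample size implies a completer analysis.* A 15% allowance is routine and names no analysis set.
- *False-positive rates rise to about 12% or 17%.* Those figures follow if there is no true effect (40% in both arms), 15% or 20% of each arm is dropped, and every patient dropped from electroacupuncture is a non-responder while sham losses are random. The section does not say that eliminated patients are dropped, and unblinded sham non-responders could as easily leave, which would bias the other way.

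**Conclusion.** The point holds as a defect of wording and conduct. Randomised patients are eliminated for post-randomisation events, their remaining scheduled outcomes are not secured, and ITT is described as an analysis on those who left and not on all randomised patients as allocated. With 15% per arm unobserved and the planned rates in the rest, the difference among all randomised patients is determined only to within 10.5 to 40.5 points. As an illustration only, counting that 15% as not effective gives ITT power of about 85% at 68 per group. That figure rests on an assumed rule and does not show an error in the sample size, which reproduces at about 90%. The actual elimination rate and its balance between arms are unknown. This is a should-fix: cheap, and worth making while outcomes can still be collected.

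**What to change.** Reword Elimination criteria to say three things:

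1. The primary analysis includes every randomised patient in the arm assigned.
2. The elimination list defines only a per-protocol sensitivity set, fixed blind to allocation before database lock.
3. Elimination or stopping study treatment does not end follow-up. VAS, pain logs and SF-36 continue at all remaining scheduled visits, by phone where needed, if the patient consents.

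Align Criteria for discontinuing the trial with this, since it repeats withdrawal and non-cooperation. Add one sentence that treatment adjustments made under Adverse event are not in themselves grounds for removal from the analysis or from follow-up; this concerns data collection and analysis only, not how patients are treated.

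The cost is a few sentences and a few extra contacts per discontinued patient. No extra patients are needed, and neither a restated power nor a particular imputation rule is required.

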### Criteria for discontinuing the trial

The trial will be discontinued if the following conditions occur: (1) patients exhibit serious adverse reactions during the study and are not suitable to continue the study; (2) patients require emergency measures for the reason that serious complications are presented or the condition is worsened during the study; (3) patients withdraw from the clinical study midway; and (4) patients do not cooperate and obey the treatment, which is not changed after repeated explanations from clinical doctors. The reasons and time for the discontinuation and withdrawal should be recorded by researchers.

### Randomization and blinding

The stratified block randomization will be taken in this study. Randomization will be stratified according to the center, and the block size is 4. Randomization is generated by SAS software (SAS Institute Inc., Cary, NC, USA), and allocation will be hidden through opaque sealed envelopes. The treatment allocation corresponding to serial no. 001–136 is listed (random coding table), and the serial number is corresponded to the number of subjects. A designated person will keep the random coding table. After subjects are selected, researchers will inform the random coding table keeper of the corresponding number of the subject. The keeper will give instructions to the subject to enter which group according to a random coding table. The researchers will record the instructions and comply with the corresponding allocation according to the instructions.

Due to the particularity of acupuncture operation, it is difficult to make operators and patients be blind. Therefore, outcome assessors and statisticians will be blind to reduce the risk of bias.

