### Sham electroacupuncture group

The bilateral sham BL33 (opening 20 mm outward at actual BL33) and bilateral sham BL34 (opening 20 mm outward at actual BL34) are selected, with shallow needling (0.35 mm × 25 mm, Jiajian Medical Equipment Co., Ltd., Wuxi, China) of 3–5 mm. The electrode placement and parameter settings of the electroacupuncture are the same as those of the electroacupuncture group, but the electricity is not turned on. After needling, there is no operation to achieve the Deqi sensation.

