### Data collection and management

A case report form (CRF) will be used to collect study-related data. The CRF must be completed for every subject by the researcher. The completed CRF will be reviewed by clinical researchers and supervisors, and then be handed over to the data administrators. Data administrators will develop the data management system according to the CRF. To ensure the accuracy of data, two data administrators will independently enter and proofread the data. For queries in the CRF, data administrators will issue an inquiry to the researchers, and correct, confirm, and enter the data based on the researchers’ answer. After confirming the accuracy of all data, the database will be locked by the main researcher, sponsor, and statistical analyst. The locked data cannot be modified.

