## Outcome measurement

### Primary outcome

#### Clinical treatment efficacy

Referring to the Guiding rules of clinical research of new Chinese medicine [14], the VAS score will be used to evaluate efficacy. VAS scores at baseline, 4 weeks and 8 weeks of treatment, and 1, 3, and 6 months of follow-up will be recorded, and clinical treatment efficacy is evaluated using the efficacy index. Efficacy index is calculated as [(pre-treatment VAS score − post-treatment VAS score) ÷ pre-treatment VAS score] × 100%. Curing is defined as the pain symptom completely disappears, and the VAS score reduction rate is ≥ 95%. Apparent effect is defined as the pain symptom broadly disappears, with occasional discomfort, and the VAS score reduction rate is ≥ 70% and < 95%. General effect is defined as the pain symptom is improved, with the non-ignorable discomfort during onset which does not affect life and work, and the VAS score reduction rate is ≥ 30% and < 70%. No effect is defined that the pain symptoms are not apparently improved, with the pain affecting life and work during onset, and the VAS score reduction rate is < 30%.

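### Patients are not blinded and rate the primary outcome themselves, so blinding assessors and statisticians does not protect the electroacupuncture–sham comparison from expectation bias

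*Protocol article*

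**What the plan says.** Under Randomization and blinding, researchers report the number of the enrolled subject to the person who holds the coding table. Then "The keeper will give instructions to the subject to enter which group according to a random coding table", after which "The researchers will record the instructions and comply with the corresponding allocation according to the instructions". The same section states that "it is difficult to make operators and patients be blind" and concludes: "Therefore, outcome assessors and statisticians will be blind to reduce the risk of bias". The Abstract also names only outcome assessors and statisticians as blind.

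Under Sham electroacupuncture group, control patients are needled shallowly, 20 mm lateral to the true points. Electrode placement and device settings match the active arm, "but the electricity is not turned on", and "there is no operation to achieve the Deqi sensation".

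Under Clinical treatment efficacy, the primary outcome, "the VAS score will be used to evaluate efficacy". The percentage fall in the VAS, together with descriptions of remaining symptoms and their effect on daily life, places each patient in one of four grades.

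The Discussion concedes that operators and patients are hard to blind and that bias may remain despite the shallow needling. It does not connect this with who rates the primary outcome.

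**The concern.** A sham with electrodes in place and the current off is there to equalise expectation between arms. It does so only to the extent that patients do not know which arm they are in. As written, the procedure sends the group instruction to the subject, and the plan does not claim patient blinding.

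The replacement safeguard does not act where the risk lies. A pain score, and a judgement of whether remaining pain disturbs life and work, come from the patient. A blinded assessor who writes the answer down cannot remove expectation from it. Blinding the statistician protects the analysis, not the measurement.

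At stake is what a significant primary result would mean. A difference in effective rates could reflect the stimulation, the patients' knowledge of their arm, or both, and the planned data would not help to separate them.

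**Working it through.** **1. The plan's own sample size.** Inputs from Sample size calculation: 70% against 40% effective, α = 0.05 (taken as two-sided), power 0.90. With the pooled-variance formula and no continuity correction,

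n = [1.96·√(2·0.55·0.45) + 1.2816·√(0.70·0.30 + 0.40·0.60)]² / 0.30² = 55.7, so 56 per group.

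The article states 57, which agrees to within one patient. Power at 57 per group is 90.7%. Dropout: 57/0.85 = 67.06, which rounds up to 68 (the article has 67). The 136 enrolled give 68 per arm, so the total is sufficient. The present point does not affect the sample size.

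**2. Who rates each outcome.**

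| Outcome | Source |
|---|---|
| Primary: VAS-based efficacy | Patient |
| Pain days per month | Patient (pain logs) |
| SF-36 | Patient |
| Anxiety and depression scales | Patient (self-rating) |
| Satisfaction | Patient (5-point Likert) |
| Anorectal manometry | Instrument; sensory thresholds depend on the patient's response |
| Pelvic floor electromyography | Instrument; contractions are voluntary |

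The primary and four of the six secondary outcomes are therefore patient-reported, five of seven in all.

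**3. What a reporting shift would do.** Assume no true effect, a 40% effective rate in both arms (the planning rate for sham), and a shift of b percentage points in the electroacupuncture arm caused only by patients knowing their group. The values of b are assumptions; the article gives no basis for any of them. The test is the two-sided pooled z test at 5%, with

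z = (p̂₁ − p̂₂) / √[p̄(1 − p̄)·2/n].

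The exact rejection probability is the sum of Bin(x₁; n, 0.40 + b)·Bin(x₂; n, 0.40) over all pairs (x₁, x₂) with |z| ≥ 1.96:

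| Assumed shift b | 68 per arm | 57 per arm |
|---|---|---|
| 0 | 4.8% | 4.8% |
| 5 points | 8.7% | 8.1% |
| 10 points | 21.0% | 18.4% |
| 15 points | 41.3% | 35.8% |

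Check by normal approximation at b = 10 points, n = 68: the null standard error is √(0.45·0.55·2/68) = 0.0853, so the critical difference is 1.96 × 0.0853 = 0.1672. The standard error under the shift is √[(0.25 + 0.24)/68] = 0.0849. Then (0.1672 − 0.10)/0.0849 = 0.79, and the two-sided rejection probability is 21.5%, in line with the exact 21.0%.

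Blinding the person who records the VAS leaves b unchanged, because b arises in the patient's answer.

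**The case against.** **The keeper sentence may be loosely worded.** The next sentence has researchers record and carry out the instruction, so they may be its intended recipients. That is a fair reading. A reader might infer that every patient is told the group, or that sham patients are told the current is off. The article does not establish either, and the consent text is not shown. The point survives, because the same section treats patient blinding as difficult and claims blinding only for assessors and statisticians.

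**Assessor blinding might seem contradicted too.** Researchers record the allocation, and "The CRF must be completed for every subject by the researcher". To infer a contradiction one must read two generic staff terms as the same person and that person as the outcome assessor. The article does not say so, and filling in a CRF is not the same as rating outcomes. For the pain logs it explicitly keeps therapists out of collection. That inference is not supported.

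**It might be tempting to say that nearly all outcomes are patient-rated.** Five of seven are. Manometry and electromyography are instrument-based, though partly dependent on the patient's response or effort.

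**The limitation is disclosed.** True in general terms. Disclosure neither reduces the bias nor tells the reader that it falls on the primary outcome.

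**Masking could fail anyway.** Needling depth, Deqi and current differ between arms and can be felt. This stands, and it argues against promising that patients are unaware. It does not argue for disclosing the allocation or for leaving patients' beliefs unmeasured.

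**Conclusion.** The concern holds in this form: the plan does not claim patient blinding, as worded sends the group instruction to the subject, and relies on blinding assessors and statisticians, which cannot protect a patient-rated primary outcome from expectation. The sham loses much of its purpose to the extent that patients know their arm.

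The size in this trial is unknown. Under the stated assumptions (no true effect, 40% in both arms, 68 per arm), shifts of 5, 10 and 15 points raise the chance of a significant result from about 5% to 9%, 21% and 41%. These shifts are at most half of the 30-point difference the trial is powered to detect. A reader might conclude that the trial cannot say anything about electroacupuncture against sham. That goes too far: the inference is weakened in proportion to a bias that nobody has measured.

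**What to change.** 1. Amend Randomization and blinding so that the keeper gives the allocation only to the treating acupuncturist, and it is not disclosed to the patient or to whoever collects the VAS and questionnaires.
2. Use neutral, ethics-approved consent wording that describes two needling procedures.
3. Add one question at week 8 asking patients which group they believe they were in, and report the answers by arm.
4. State that the primary outcome is patient-reported, that patient masking is attempted but may be incomplete because Deqi, depth and current differ between arms, and that assessor blinding alone does not protect it. Carry the same statement into the limitations in the Discussion.

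Cost: a consent and ethics amendment, a changed allocation procedure and one extra CRF item. Sample size and treatments are untouched. Some patients will still guess their group; the added question shows how many.
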